#### Additional variables

*Parent Attendance* will be assessed by the group facilitator taking attendance of both mothers and fathers at the group sessions. This will only be assessed for parents in the intervention group. It will be coded as either present or not present for both mothers and fathers.

The *Conflicting Advice Questionnaire* and *Problem Solving* is a 6­item measure that was developed for this study to assess the extent participants received conflicting information or advice from professionals and from family and friends, as well as how they deal with confusion and problems. First, it asks about the extent of confusion in regards to five areas, separately from professionals, and from friends and family: feeding the baby, settling the baby, putting the baby to sleep, bathing the baby and dressing and changing the baby. Then, participants are asked to write about any other topics where they experience confusion. Next, participants are asked about what they do when they are confused or encounter a problem in regards to their baby. They can tick one or more of the following options: seek out additional information from family, seek out additional information from professionals, research the internet, corroborate with partner about the problem and try to think of a solution together, try out different strategies until one works. The final item allows participants to write about any other problem solving strategies they have been using.

##### Strategies checklist

This checklist asks parents to indicate which of the 29 strategies that are taught in the Baby Triple P program they have used since their baby was born. The response options include *not at all, a little bit, sometimes, a lot* and *all the time.* This measure was specifically created for this study.

##### Services accessed

Parents will be asked which services they have accessed since they had their baby. Ten options will be listed and participants are asked to tick the service they used, how many times they used it, what they used the service for and how helpful they found it (*very, somewhat, not helpful*).

The *Client Satisfaction Questionnaire* [55, 83] is an 8­item questionnaire that assesses participant’s perception of the quality of the program received, how well the program addresses their needs as well as their overall satisfaction with the services provided. Only the Baby Triple P group completed this measure.

## Statistical analyses

Prior to conducting the main analyses, data will be screened for distributional assumptions (e.g., univariate and multivariate normality, outliers and multi-collinearity) as well as inter- and intra-measure consistency. Preliminary analyses will also investigate whether the study groups differ on any demographic characteristics at baseline. This will be examined via linear (for continuous outcomes) and logistic (for categorical outcomes) regression models. If baseline group differences are detected, we will investigate and report the extent to which the results from the planned analyses described below are altered, when these differences are statically controlled. For missing data points, an analysis of missing data will be conducted (see paragraph below on missing data) and imputation methods will be considered.

### Primary analyses

The analyses will evaluate the effects of the intervention on parent and baby outcomes, including the primary outcome measures of parenting confidence and sense of competency. These analyses will include self-reports obtained from parents as well as reports on baby behaviors, baby diaries and observational assessment. A multilevel modeling approach will be used to take into account the repeated measurements and thus non-independence of observations [84]. This approach will be used for variables that have three measurement time points (e.g. Couple Relationship and the EPDS). Dummy codes contrasting the groups will serve as fixed effects, allowing for random intercepts and slopes to vary across individuals. Outcome variables with two time points (e.g., MSES, and the Baby Diary) will be analyzed using a series of rANOVAs and rMANOVAs. The primary analyses will be conducted for mother and father data separately to investigate whether the intervention is beneficial for both parents, or has different effects for mothers and fathers. Significant fixed effects contrasting Baby Triple P with CAU will indicate whether the intervention is an improvement over usual care. Separate models will be estimated for each outcome measure using Bonferroni correction to control for inflation of Type 1 error due to multiple comparisons.

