#### Randomization

Participant randomization to either the Baby Triple P or CAU group will be conducted by generating a random allocation sequence, by a researcher not involved in the project, using a computer-based random number generator. A pre-prepared series of sealed opaque envelopes, each labelled with a participant ID number, will conceal group allocation from researchers and participants until after completion of the baseline assessment. Immediately after completion of the baseline questionnaires, the research coordinator will open the envelope, and will notify participants of their condition allocation via phone.

Participants allocated to the intervention condition will attend group sessions based on their preference for day and time, depending on availability of groups. Participants will be allocated to groups as soon as possible after randomization. Figure 1 summarizes the flow of participants through the study.

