### Intervention

The intervention will consist of four, 2-h *Baby Triple P* group sessions conducted during pregnancy, followed by four individual 30-min telephone sessions conducted postnatally. The program is based on the same theoretical principles that underpin the Triple P system [6] and sessions are interactive and allow opportunities for discussion.

Baby Triple P is an eight-session psychological intervention, developed by Spry (2013) that aims to prepare couples for a positive transition to parenthood by teaching them core skills in the domains of parenting their baby, taking care of their own wellbeing and maintaining a positive relationship with their partner. The self-regulatory framework will be used to engage participants and facilitate learning. Specifically, it includes active training methods, for example modelling, rehearsal, practice, feedback and goal setting. These techniques are aimed at teaching specific skills and promoting parental competence. The intervention was developed on the basis of a review of the scientific literature outlining the key risk and protective factors for both parents and infants and includes teaching parenting strategies (Sessions 1 & 2), individual coping skills (Session 3) and partner support skills (Session 4).

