The parenting strategies are designed to promote a warm and responsive relationship between parents and their babies as well as promoting a positive learning environment for the infant. These first four sessions are conducted in a group setting. Specific parenting strategies covered include spending quality time, affection, settling strategies and providing a stimulating and engaging environment. Individual coping skills taught include acceptance, identifying the relationship between thoughts and emotions, using coping statements, abdominal breathing, being involved in pleasant activities, and developing coping plans. As part of the partner support skills session, couples learn positive speaking and listening skills, casual conversations, communicating their emotional experience and spending quality time together. Throughout the group sessions, parents are given information about common experiences of new parents both at an individual as well as on a couple level. This information aims to promote realistic expectations about the changes that come with the transition to parenthood. Parents further learn how to apply parenting strategies appropriately across the different developmental milestones of the infant. During Session 1, parents are provided with a copy of the Baby Triple P workbook which they could take home and review the content in their own time.

The content is followed up with four postnatal individual telephone sessions (Sessions 5 to 8), which employ a self-regulatory model. The telephone sessions review homework from a previous session, focussing on strengths and areas to improve, and setting and monitoring goals for areas of future change. This teaches participants to reflect on their own behavior as well as the impact it has on their baby. Both the prenatal group sessions and the telephone sessions will be delivered by the first author and trained interns in clinical psychology.

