### Care as usual

Couples in CAU will complete assessments at baseline, ten weeks post birth, and at six months post birth. These are the same time points at which the intervention group complete their assessments. During this time, families will continue to receive regular primary care and other pre and post-natal services, as appropriate, including antenatal classes, which may be offered at the mother’s hospital, as well as other services provided by GPs or obstetricians. These services were also available to mothers in the Baby Triple P group. Other than regarding issues of assessment, these parents will have no contact with the research team, but are free to access support from other community services and will be given appropriate referral information should they ask for assistance. After the 6-month follow-up assessment, families will be offered the Baby Triple P workbook.

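### The intervention is delivered in groups in one arm only, but the stated models have no group level; if shared sessions make outcomes alike, the treatment-effect standard error is understated

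*Protocol article*

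**What the plan says.** On delivery, the Intervention section says of the antenatal part: "These first four sessions are conducted in a group setting". The rest of the programme is individual: "followed by four individual 30-min telephone sessions conducted postnatally". Both parts "will be delivered by the first author and trained interns in clinical psychology". Under Randomization, couples are allocated first and then choose: "Participants allocated to the intervention condition will attend group sessions based on their preference for day and time, depending on availability of groups". Under Care as usual, apart from assessment, "these parents will have no contact with the research team". Only one arm therefore has a shared delivery structure. The article gives neither the number nor the size of the groups.

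On analysis, Primary analyses introduces the multilevel model for a single source of dependence: "A multilevel modeling approach will be used to take into account the repeated measurements and thus non-independence of observations". Its terms are: "Dummy codes contrasting the groups will serve as fixed effects, allowing for random intercepts and slopes to vary across individuals". The word groups there means the trial arms, because the section goes on to interpret the fixed effects as Baby Triple P against usual care. Outcomes with two time points, with the Maternal Self-Efficacy Scale (MSES) as an example, go to repeated-measures ANOVA or MANOVA. Mothers and fathers are analysed separately. The sample size section makes no allowance for clustering.

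**The concern.** This is a partially nested design: couples in one arm are clustered in parenting groups and couples in the other are not. The sessions are interactive, so a good or poor facilitator, or a supportive or difficult set of peers, can move everyone in a group the same way. The plan recognises non-independence but names only repeated measurement as its source.

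Where such a group effect exists, the intervention-arm mean varies more than the model believes. Confidence intervals are then too narrow and p-values too small, for both primary outcomes among others. Bonferroni correction does not repair this, because each p-value going into it is already too small. Separate models for mothers and fathers keep within-couple dependence out of each model but leave within-group dependence in place.

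**Working it through.** **The article's own figure.** Stated inputs: ES 0.5, 80% power, two-sided alpha .05, within-between interaction, correlation .5, giving N = 80. Reading ES 0.5 as f = 0.25 for two equal arms, with t time points and noncentrality λ = f²·N·t/(1 − ρ), the required N is 34 for t = 2 and 28 for t = 3. The between-arm test, λ = f²·N·t/(1 + (t − 1)ρ), needs 98 or 86. So 80 does not follow from the stated inputs. That is a separate matter; 80 is taken as given below. Attrition: 80/0.8 = 100 to recruit. The planned 110 leaves 110 × 0.8 = 88 evaluable, a margin of 8.

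**Assumptions, because the article gives no values.** m = 4 to 10 couples per group; session-induced ICC = .01 to .10; equal arms; one analysed parent per couple, so the cluster size is m.

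**Formulas, for the arm contrast after baseline.**
- Design effect in the intervention arm: DE = 1 + (m − 1)·ICC. In usual care it is 1.
- Variance ratio of the arm difference: V = (DE + 1)/2. Standard error ratio = √V.
- Actual type I error: 2·P(Z > 1.96/√V).
- Evaluable N for 80% power: 80·V, rounded up. Recruited N: that figure divided by 0.8.
- Power with 88 evaluable: Φ[(1.96 + 0.8416)·√(88/80)/√V − 1.96].

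| m | ICC | DE | V | SE ratio | Type I error | Evaluable N | Recruited N | Power at 88 |
|---|---|---|---|---|---|---|---|---|
| 4 | .01 | 1.03 | 1.015 | 1.007 | .052 | 82 | 103 | .831 |
| 4 | .05 | 1.15 | 1.075 | 1.037 | .059 | 86 | 108 | .809 |
| 8 | .01 | 1.07 | 1.035 | 1.017 | .054 | 83 | 104 | .823 |
| 8 | .05 | 1.35 | 1.175 | 1.084 | .071 | 94 | 118 | .774 |
| 8 | .10 | 1.70 | 1.350 | 1.162 | .092 | 108 | 135 | .715 |
| 10 | .10 | 1.90 | 1.450 | 1.204 | .104 | 116 | 145 | .684 |

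**Break-even for power.** The margin of 8 is used up when V = 88/80 = 1.10, that is, when (m − 1)·ICC = 0.20. Five couples per group at ICC .05 sits exactly there (4 × .05 = 0.20).

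**Simulation check.** With 44 per arm, 40,000 runs and a test that ignores groups, type I error was .057 (m = 4, ICC .05), .069 (m = 8, ICC .05) and .090 (m = 8, ICC .10). With ICC 0 it was between .048 and .052. This agrees with the formulas.

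**The case against.** **The consequence is conditional.** A reader might infer that the standard errors are certainly too small and that the type I error certainly exceeds .05. The article does not support that. It gives no ICC, and at ICC .01 with four couples per group the inflation is negligible (.052). If the programme affects nobody, individual randomisation keeps the ordinary test valid. The inflated error rates describe the case where groups differ in what they deliver but those effects average to zero. This objection stands, and it limits the claim.

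**Choice of session.** A reader might also infer that self-selected session times inflate the error. They do not by themselves. Couples are randomised individually before they choose, and sorting couples already allocated does not change the variance of the arm mean. A simulation with 48 per arm, sorted into groups of six on a covariate, had a mean ICC of .098 and a type I error of .050. Only effects created by the sessions count.

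**Dilution.** Half of the eight sessions are individual telephone calls, which may weaken the group effect. That is fair, although the same few facilitators deliver the calls as well and may add correlation of their own.

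**Power.** At four couples and ICC .05, 108 families are needed and 110 are planned, so nothing is lost there. A general claim of lost power would go too far.

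**Condensed article.** A full analysis plan might add a group term, and the article does not say that individuals are the only level. But it does state a random-effects structure and the reason for it, and that structure omits a level that its own Intervention section describes. This is more than silence on a detail.

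**Conclusion.** The point holds in conditional form. The stated models ignore a level of dependence that the design can create in one arm. If the session-induced ICC is positive, the standard error of the treatment effect is understated. Over the assumed range, the true standard error is about 1% to 20% larger than the reported one, and type I error at nominal .05 is about .052 to .104. The evaluable N for 80% power is about 82 to 116 against 88 expected, so power drops below target only when (m − 1)·ICC exceeds 0.20.

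These figures rest on assumed group sizes and ICCs, on equal arms, on a normal approximation, and on the article's N of 80. The omission can be read from the article; its size cannot. The analysis can still be changed: the Discussion says that follow-up is complete and that results will appear once the analyses are finished.

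**What to change.** Identify the parenting group of each intervention couple. Additional variables says that facilitators take attendance at group sessions, so membership should be recoverable even though data collection has ended. Then fit partially nested mixed models with Satterthwaite or Kenward-Roger degrees of freedom, each usual-care couple standing as its own unit:

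- **Outcomes measured only at T2 and T3, such as the MSES:** replace repeated-measures ANOVA with a mixed model that has a random intercept for parenting group in the intervention arm only.
- **Outcomes with a T1 baseline, such as the Maternal Self-Report Inventory:** let the group effect act only after baseline, through a group-by-time random term or by modelling T2 and T3 adjusted for T1. A constant group intercept is wrong here. No group exists at T1, and a constant term cancels from the arm-by-time effect. In simulation, a constant group effect at ICC .10 left the change-score test at .051, so such a term has nothing to correct.

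Report the estimated group variance or ICC with its uncertainty.

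The cost is fewer degrees of freedom, slightly wider intervals and an imprecise group variance. With groups of 4 to 8 there would be roughly 6 groups (44 evaluable intervention couples, 44/8) to 14 groups (55 randomised, 55/4), and fewer still with groups of 10. No new data collection should be needed.

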## Aims and hypotheses

In light of the critical importance of a successful transition to parenthood it is clear that strategies need to be developed to support families and enhance the protective factors for babies to ensure positive developmental outcomes. This is vitally important especially for those families with identified risk factors who may find the transition to parenthood particularly challenging. The proposed research will evaluate the efficacy of a tailored parenting intervention, Baby Triple P that combines parenting information, with the provision of strategies to enhance individual wellbeing and couple adjustment for high­risk families.

The aim of this study is to experimentally test the hypothesis that provision of parenting support at the transition to parenthood through Baby Triple P, will lead to improvements in parental confidence and sense of competence in their abilities as parents. Furthermore, we will test the secondary hypotheses that the program will lead to higher levels of responsiveness and bonding with the baby, higher relationship happiness, higher levels of life satisfaction, fewer instances of depression, anxiety and stress, and infants would show less fussing or crying and fewer sleeping problems. It is hypothesized that these positive treatment effects will be maintained at six-month-follow up.

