### Assessment

Table 1 provides an overview of the assessment measures and the time points at which they are assessed. All parent-report measures will be provided in a written (online or printed) self-administered questionnaire format, and will take approximately 30 to 40 min to complete. Most of the measures used have been previously validated and are commonly used. Socioeconomic status (e.g., income, occupation status, parent education), age, history of mental illness and ethnic background will be assessed using the *Family Background Questionnaire* [61]*.* Only the mother will complete this measure, as well as the *Cambridge Worry Scale* [CWS; 68].

**Table 1 Tab1:** Summary of Assessment Measures

Construct	Assessment Measure	Time Point
Demographics	*Family Background Questionnaire*	T1
Primary Outcomes		
Parental Confidence	*Maternal Self-Report Inventory*	T1, T2, T3
Parental Self-Efficacy	*Maternal Efficacy Questionnaire*	T2, T3
Secondary Outcomes		
Parental Mental Health		
Depression	*Edinburgh Postnatal Depression Inventory*	T1, T2, T3
Anxiety	*Depression Anxiety Stress Scale 21*	T1, T2, T3
Pregnancy Worry (mothers only)	*Cambridge Worry Scale*	T1, T2, T3
Life Satisfaction	*Oxford Happiness Questionnaire*	T1, T2, T3
Expectations	*Prenatal Maternal Expectations Scale*	T1
Family and Social Support		
Couple Relationship	*3 items from PAFAS, 2 items from HCTC & 1 overall item*	T1, T2, T3
Social Support	*Social Support Scale*	T1
Mother-Child Relationship		
Maternal Responsiveness	*Maternal Infant Responsiveness Inventory*	T2, T3
Observed Mother-Infant Responsiveness	*The Care Index*	T2, T3
Mother-Child Bonding	*Postpartum Bonding Instrument*	T2, T3
Baby Outcomes		
Problematic Behaviors	*Baby Behaviour Inventory*	T2, T3
Baby Behaviors	*Baby Diary*	T2, T3
Other		
Parent Involvement	*Attendance at group sessions (intervention only)*	During group sessions
Conflicting Advice & Problem Solving	*6 items*	T1, T2, T3 (problem solving only T2 and T3)
Strategies used	*Strategies Checklist*	T2 (intervention only), T3
Services accessed		T2, T3
Client Satisfaction	*Client Satisfaction Scale*	T2

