### Sample size and power analysis

The required sample size for the study was calculated to assure 80% power to detect a medium effect size (ES) = 0.5 for a mean difference in the variables of interest between the groups (INT vs CAU). Effect sizes for early intervention studies range from small to large on a range of outcomes [48]. Two studies that assessed parental confidence and competence as an outcome of a parenting intervention found a small [85] and a large [43] effect. Given these are our primary outcome measures, a medium effect size was expected in this study. Furthermore, as our study will recruit an at-risk sample, an expected medium effect is a conservative estimate. We performed power analysis using G*Power software [86] for rANOVA, looking at the within-between interactions and allowing for conservative estimate of intra-individual variability (.5). The analyses indicated that a sample size of 80 is sufficient to detect an ES of 0.5 at the significance level of .05 (two-tailed). This is without taking into account the added power accorded by the rich repeated measures in our data. In multilevel models with repeated measures, the sample size is effectively the number of observations (level-1), not number of participants (level-2 units). Assuming a 20% attrition rate (based on estimate within Bakermans-Kranenburg, van Ijzendoorn [46] review), an available sample of 110 families will be sufficient to detect medium sized effects.

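### The stated 80% power does not carry over to the co-primary self-efficacy scale, which has no pre-test, and the rANOVA term that decides that outcome is not fixed

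*Protocol article*

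**What the plan says.** Table 1 (Assessment) lists two primary outcomes. The Maternal Self-Report Inventory is scheduled at T1, T2 and T3. The self-efficacy measure, there called the "Maternal Efficacy Questionnaire", is scheduled at T2 and T3 only. Primary outcome measures describes it as the Maternal Self-Efficacy Scale (MSES); I take the two names as one instrument.

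For the analysis, Primary analyses says: "Outcome variables with two time points (e.g., MSES, and the Baby Diary) will be analyzed using a series of rANOVAs and rMANOVAs". Its criterion for success is: "Significant fixed effects contrasting Baby Triple P with CAU will indicate whether the intervention is an improvement over usual care". Bonferroni correction is to apply across outcomes, and mothers and fathers are analysed separately.

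Sample size and power analysis sets the target as 80% power for a between-group mean difference of 0.5. It then describes the calculation as a rANOVA "looking at the within-between interactions and allowing for conservative estimate of intra-individual variability (.5"), which gives 80, or 110 families after 20% attrition. Design describes two groups by three times, the first being a pre-test. Aims and hypotheses expects that "these positive treatment effects will be maintained at six-month-follow up".

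**The concern.** These statements fit together for an outcome with a pre-test but not for the MSES. Both MSES visits come after the group sessions. The group-by-time term therefore compares the T2-to-T3 change between arms and does not estimate the benefit of the programme. A benefit reached by 10 weeks and held to 6 months leaves that term at zero, while a benefit that fades makes it significant.

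Two things are at stake. The power claim covers all variables of interest, so a reader will take it to cover this primary outcome. And because no rANOVA term is fixed for the MSES, the deciding term could be chosen after the arms have been compared.

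**Working it through.** **Inputs.** From Sample size and power analysis: ES 0.5, read as d = 0.5 (f = 0.25); two-sided alpha .05; N = 80; 110 families with 20% attrition, so 110 × 0.8 = 88 completers, 44 per arm. Assumptions: the stated .5 is the correlation r between visits (range .3 to .7 shown); Bonferroni covers two tests, so .05/2 = .025.

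**1. The plan's own figure.** Noncentral F for the interaction, 2 groups, m visits:

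| Noncentrality | m = 3 | m = 2 |
|---|---|---|
| f² × N × (m − 1), .5 not used | N = 80 | N = 128 |
| f² × N × m / (1 − r), r = .5 | N = 28 | N = 34 |

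Of the variants tried at f = 0.25, only the three-visit interaction in the first row gives 80: noncentrality 0.0625 × 80 × 2 = 10, power 81%; N = 78 gives just under 80%. The MSES has two visits, and the same formula then gives 128. A group main effect with r = .5 gives 86 for three visits and 98 for two.

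**2. What each MSES term tests.** Let d2 and d3 be the arm differences at T2 and T3, in SD units.
- Interaction: estimates d3 − d2, with variance per person 2 − 2r = 1 at r = .5.
- Group effect: estimates (d2 + d3)/2, with variance per person (1 + r)/2 = 0.75 at r = .5.

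Power is from the noncentral t with 86 df and noncentrality (effect/√variance) × √(44/2). For the maintained benefit the group effect has 0.5/√0.75 = 0.577, and 0.577 × √22 = 2.71.

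| True d2, d3 (r = .5, alpha .05, 88 completers) | Interaction | Group effect |
|---|---|---|
| 0.5, 0.5 (maintained) | 5% | 76% |
| 0.5, 0.25 (halved) | 21% | 52% |
| 0.5, 0 (lost) | 64% | 27% |

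A simulation of 20,000 trials gave 4.9%, 21% and 64% for the interaction, and 76%, 52% and 26% for the group effect. Under a maintained benefit the interaction rejects at alpha whatever r is.

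**3. Power for the group effect, benefit maintained.**
- Alpha .05: 82% at r = .3, 76% at r = .5, 71% at r = .7.
- Alpha .025, r = .5: 66.5%, about 67%.
- For 80% at r = .5: 98 analysed at .05 (98/0.8 = 122.5, so 123 families), or 118 at .025 (118/0.8 = 147.5, so 148 families).

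**4. Possible gain from a T1 covariate.** If the T1 Maternal Self-Report Inventory score correlates b with each later MSES score, the variance falls to 0.75 − b². At alpha .05, b = .3 gives 0.66, noncentrality 2.89 and 81% power; b = .5 gives 0.50, noncentrality 3.32 and 91%. The documents do not give b.

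**The case against.** The strongest reply is that nothing in the article makes the interaction the MSES test. The success criterion under Primary analyses is a contrast of Baby Triple P with CAU. The power section states its target as a between-group mean difference. The Abstract also lists t-tests, and a 2 × 2 rANOVA yields a group main effect as well as an interaction. The interaction appears only as the planning basis, presumably for the 2 × 3 design that the other primary measure follows.

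This stands. A reader might infer that the MSES will be judged on the interaction and so will miss a maintained benefit. The documents do not say that, and the 5% figure applies only if that term were chosen. What remains is that the criterion is in mixed-model language, the t-tests are not assigned to any outcome, and the one rANOVA term named is unsuitable for the MSES.

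Three further replies also stand. The absence of an MSES baseline is not a defect: the items concern soothing, feeding and bathing a baby already born, and randomisation makes a post-birth comparison valid. For a group effect a higher r lowers power, but this does not show the stated .5 to be an error, since the article calls it variability and 80 reproduces without it. Multiple imputation with rANOVA is legitimate.

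**Conclusion.** The point holds in a limited form. The statement that 80 analysed give 80% power does not apply to one of the two primary outcomes as it is scheduled, and the term that decides that outcome is not fixed. On the favourable reading, that the group effect is tested, 88 completers give about 76% at alpha .05, a modest shortfall. The Bonferroni correction that the plan itself requires takes this to about 67% if it covers two tests, and lower if it covers more.

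These figures assume d = 0.5 at both visits, r = .5 between visits and no covariate. The other primary measure has a T1 value, so this problem does not arise for it.

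**What to change.** Under Primary analyses, state that the MSES primary test, for mothers and for fathers, is the between-group effect averaged over T2 and T3, adjusted for the same parent's T1 Maternal Self-Report Inventory score. State that group-by-time for the MSES is reported only to address whether the effect is maintained.

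Under Sample size and power analysis, restate the power for that contrast at the Bonferroni-corrected alpha, giving the number of tests and the assumed between-visit correlation. The covariate's gain depends on an unknown correlation, so show the power without it as the base case. Averaging over visits loses power if the benefit fades (second table above), and the text should accept this openly.

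The cost is wording only, since the T1 score is already collected. The article reports recruitment closed and follow-up complete, so the sample size cannot change; the term should be fixed before the arms are compared. Replacing multiple imputation or adding the EPDS as a covariate is optional and not needed to cure this.
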